### Outcomes {12}

The primary outcome parameter of this study is a composite endpoint consisting of (1) severe hemorrhagic complications according to the ELSO definitions: clinically overt bleeding with a transfusion requirement of more than 20 ml/kg red blood cell (RBC) transfusions or >3U RBC in one calendar day. Bleeding that is retroperitoneal or pulmonary or involves the central nervous system or bleeding that requires surgical intervention will also be considered major bleeding; (2) severe thromboembolic complication defined as ischemic stroke, limb ischemia, or acute pump failure; (3) mortality at 6 months. This composite outcome was designed to capture the net clinical effect of reduced anticoagulation targets, e.g., a reduction of major bleeding not counteracted by an increase in thromboembolic complications. Mortality is part of the composite outcome to capture unknown or unmeasured effects of reduced anticoagulation.

Secondary endpoints are all other variables that may be affected by the anticoagulation regime: (1) blood transfusions, (2) quality of life (HR-QoL) at 6 months, (3) exchange of the membrane oxygenator, (4) vessel thrombosis after ECMO removal detected by echography, (5) pulmonary embolism, (6) costs, (7) the individual components of the composite outcome, (8) all thromboembolic complications combined, and (9) all hemorrhagic complications combined.

### Participant timeline {13}

See the flowchart in Fig. 1.

**Fig. 1 Fig1:**
[figure not shown]
Flowchart. Decision tree randomization and crossover

### Sample size {14}

We expect that with a target of 1.5–2.0× baseline aPTT or with LMWH the primary composite endpoint will be reached in 60% of patients compared to 70% in usual care. To show non-inferiority with a significance level (alpha) of 5%, power of 80%, and a non-inferiority limit (delta) of 7.5%, the corresponding sample size is 91 patients per group. In other words, if there is a true difference in favor of the experimental treatment of 10%, then 91 patients per group are required to be 80% sure that the upper limit of a one-sided 95% confidence interval (or equivalently a 90% two-sided confidence interval) will exclude a difference in favor of the standard group of more than 7.5%, thus 75.25% in the intervention groups compared to 70% in usual care. To compensate for a lower effect and drop-outs, 330 patients will be enrolled. Drop-outs are defined as the withdrawal of informed consent or loss to follow-up.

### Recruitment {15}

All adult patients who receive ECMO treatment during the study period in one of the participating centers can be considered for enrolment; they will be included and randomized by local investigators. As previously mentioned, on-site kick-off meetings are planned before the start of recruitment with the local investigators, research nurses, and treating physicians to explain our hypothesis and the need for this study and will be repeated yearly, to improve recruitment.

## Assignment of interventions: allocation

### Sequence generation {16a}

All patients who receive ECMO treatment during the study period in one of the participating centers can be considered for enrolment in the study. Randomization will be 1:1:1, using variable block size and stratified by ECMO mode and study site.

### Concealment mechanism {16b}

Randomization will be performed if the subject meets all inclusion and exclusion criteria and will be processed centrally using a web-based system that will provide the randomization treatment arm (a target of 2–2.5× baseline aPTT, 1.5–2.0×, or therapeutic LMWH). The online system (ALEA Research®) is constructed and validated for randomization and data management and has an audit trail.

### Implementation {16c}

Contact persons of all participating centers can sign in to the web-based randomization system and randomize their patients. Patients will be automatically allocated to one of the anticoagulation regimes by the system.

## Assignment of interventions: blinding

### Who will be blinded {17a}

In this single-blind open-label study, only the patient will be blinded for the allocation. Outcome assessment and statistical analysis will be done blinded for treatment allocation.

### Procedure for unblinding if needed {17b}

As the design is open-label, that is single-blind, no indications for breaking the randomization code are provided in the protocol. Randomization is communicated with the local principal investigator of each participating hospital who further carries out the necessary arrangements. Based on the aPTT levels achieved concealed allocation can be controlled.

## Data collection and management

### Plans for assessment and collection of outcomes {18a}

Data will be collected and stored as described at point 19. Data will be collected from the patients’ medical files and entered into the eCRF. After 6 months, patients who are still alive will be contacted by phone for health-related quality of life questionnaire (EQ-5D-5L). The EQ-5D-5L questionnaire consists of 5 questions in 5 domains: mobility, self-care, usual activities, pain/discomfort, and anxiety/depression. Each dimension has 5 levels. The answers to this questionnaire result in a 5-digit number that describes the patients’ health state. Another part of the questionnaire is the EQ-VAS which records the patients’ self rated-health on a scale from 0 to 100. The EQ-5D is the most widely used health-related quality of life questionnaire in health economic evaluations [11].

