#### Secondary study parameters

For secondary outcome measures, between-group differences will be analyzed using independent samples *t*-tests, chi-square test, or Mann-Whitney tests, where appropriate and adjusted for center and ECMO mode. If necessary, multivariable regression analysis will be used to adjust for imbalances in main prognostic variables between the intervention and control groups.

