### Adverse event reporting and harms {22}

Clinical research involving critically ill patients illustrates several concerns with the existing system for monitoring adverse events.

Morbidity and mortality rates are high among patients in the ICU. In this particular study population, mortality rates exceed 50% [12]. Therefore, whether enrolled in a trial or not, ICU patients are particularly likely to experience clinical events that fall within the definition of a serious adverse event. These events include death, nosocomial infection, and laboratory test results indicating potentially dangerous physiologic abnormalities. Thus, a high proportion of ICU patients may experience a serious adverse event.

We clearly described the SAEs we plan to identify and label these as primary and secondary outcomes. These outcomes will be reported in the CRF and do not have to be reported separately. Periodic reports of SAEs will be reported through an Internet portal for submission, review, registration, and publication of medical research involving human subjects, to the accredited MREC that approved the protocol and the safety committee. Since case fatality in the patient population under study is known to be around 50%, a line listing of patients that have met the primary endpoint including deaths will be performed, with reporting once per 3 months. This reporting will be the responsibility of the study coordinator and the primary investigator. Other SAE’s then the outcome measures can be spontaneously reported in the CRF if serious and possible occur as a consequence of the study and will also be included in the 3 monthly line listing report.

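### Six-month quality of life is collected only from survivors although about half the patients die, so the planned group comparison can hide or distort a survival benefit

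*Protocol article*

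**What the plan says.** All references are to the protocol article.

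- Outcomes {12} lists the endpoint among the secondary endpoints: "2) quality of life (HR-QoL) at 6 months".
- Plans for assessment and collection of outcomes {18a} states who supplies the data: "After 6 months, patients who are still alive will be contacted by phone for health-related quality of life questionnaire (EQ-5D-5L"). The EQ-VAS is part of the same questionnaire.
- Secondary study parameters gives the analysis: "between-group differences will be analyzed using independent samples *t*-tests, chi-square test, or Mann-Whitney tests, where appropriate and adjusted for center and ECMO mode". The next sentence adds: "If necessary, multivariable regression analysis will be used to adjust for imbalances in main prognostic variables between the intervention and control groups".
- Adverse event reporting and harms {22} describes mortality twice: "In this particular study population, mortality rates exceed 50" per cent, and "Since case fatality in the patient population under study is known to be around 50" per cent.
- Objectives {7} expects survival to improve with both interventions but gives no size. The Discussion also expects better quality of life at 6 months.
- Cost-effectiveness analyses plans QALYs from EQ-5D-5L utilities. Outside that analysis, nothing says how a death enters a quality-of-life comparison.

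**The concern.** Only living patients can answer a questionnaire, so the collection rule is unavoidable. The problem arises when that rule meets the stated tests. A t-test or Mann-Whitney test on the questionnaires obtained compares the survivors of one arm with the survivors of another. Survival is determined after randomisation, is part of the primary endpoint, and is expected to differ between arms. The two survivor groups need not be alike, and randomisation does not protect the comparison.

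If a strategy keeps alive patients who would otherwise have died, those patients enter its quality-of-life mean and have no counterpart in the control mean. If they are more impaired than the rest, the better strategy has the lower mean. If they are equally well, the means agree and the benefit does not show. The Discussion anticipates improved quality of life, so a conclusion is likely to be drawn from this endpoint.

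**Working it through.** **The plan's own figure.** No sample size is given for quality of life. The figure for the primary endpoint (Sample size {14}) reproduces. With event rates of 70% and 60%, a margin of 7.5%, one-sided alpha of 5% and power of 80%:

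n = (1.645 + 0.842)² × (0.70×0.30 + 0.60×0.40) / (0.10 + 0.075)² = 6.183 × 0.45 / 0.0306 ≈ 90.9, so 91 per group.

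Enrolment of 330 at 1:1:1 gives 110 per arm. At 50% mortality about 55 per arm, or 165 in all, could supply a questionnaire.

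**Effect of restricting to survivors.** Assumed inputs, none of them in the article:

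- survival s₀ = 0.50 in control, in line with the stated mortality of about 50%;
- survival s₁ = 0.60 with the intervention;
- utility u₀ = 0.70 in patients who survive under either strategy, the same in both arms;
- utility u in the additional survivors, varied from 0.3 to 0.7.

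Formulas:

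- survivors only: D_S = (s₁ − s₀)(u − u₀)/s₁ = 0.1(u − 0.70)/0.6
- all randomised, death = 0: D_A = (s₁ − s₀)u = 0.1u

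For u = 0.4, the intervention survivor mean is (0.50×0.70 + 0.10×0.40)/0.60 = 0.65, so D_S = 0.65 − 0.70 = −0.05. With death = 0 the means are 0.39 and 0.35, so D_A = +0.04.

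| u | D_S | D_A |
|---|---|---|
| 0.3 | −0.067 | +0.030 |
| 0.4 | −0.050 | +0.040 |
| 0.5 | −0.033 | +0.050 |
| 0.7 | 0.000 | +0.070 |

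The signs are opposite for every u between 0 and 0.70. At u = 0.70 there is no reversal, but the survivor comparison shows nothing. With a smaller survival gain (s₁ = 0.55) and u = 0.4, D_S = 0.05 × (−0.30)/0.55 = −0.027 and D_A = 0.05 × 0.4 = +0.020.

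**Size relative to chance.** This used 5,000 simulated two-arm trials per row, with 110 per arm, an assumed SD of 0.25, utilities truncated to the range −0.4 to 1, and an unadjusted t-test in survivors at two-sided 5%.

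| Survival | u | Survivor mean lower in intervention arm | Significantly worse | D_A below 0 |
|---|---|---|---|---|
| 60% vs 50% | 0.3 | 92% | 28% | 28% |
| 60% vs 50% | 0.4 | 86% | 19% | 22% |
| 60% vs 50% | 0.5 | 75% | 10% | 16% |
| 60% vs 50% | 0.7 | 49% | 2.6% | 9.5% |
| 55% vs 50% | 0.4 | 71% | 9% | 35% |

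The all-randomised difference favours the intervention on average in every row, though not in every single trial. In the first three rows and the last, the survivor-only difference points the other way on average.

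**The case against.** **Silence on deaths is not an error.** The article nowhere says that the comparison is restricted to survivors. A reader might infer that from the collection rule and the tests taken together, but an analysis plan that is not shown could assign deaths a value or rank. This stands: the absence of such a rule from a condensed article is not itself a fault. What remains is the consequence of the collection rule and tests that the article does state, if they are applied as they read.

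**The survival effect is visible elsewhere.** Mortality is in the primary composite and, as an individual component, is also a secondary endpoint. QALYs combine survival and utility. This limits the harm, since a survival gain would be reported beside the quality-of-life result. It does not repair the separate quality-of-life endpoint.

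**The reversal is assumed.** A reader might conclude that a life-saving strategy would look worse. The documents do not support that: they give no utilities and no size for the survival effect, and the only 10-point difference they state is for the composite. With equal utility in the additional survivors there is no reversal. Even under the less favourable assumptions, a significantly worse result appears in a minority of simulated trials.

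**Quality of life among survivors is a legitimate question.** It is, and it should still be reported. Scoring death as 0 is a different estimand that partly repeats mortality and overlaps with the QALY analysis.

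**Adjustment.** A reader might also infer that the named tests cannot be adjusted, or that the stratification will be ignored. The article states adjustment for center and ECMO mode unconditionally. The if-necessary sentence concerns other prognostic variables. Stratified or model-based counterparts of all three tests exist, so this is loose wording only.

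**Conclusion.** The point holds in a limited form. With EQ-5D-5L collected from survivors only, mortality around 50% and simple two-group tests, the plan as written compares about half of each arm, selected by a post-randomisation outcome that the trial expects treatment to change. A survival benefit would be hidden or, if the additional survivors have lower utility, would appear as worse quality of life.

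Under the 50% versus 60% survival scenario, the gap between the two analyses is 0.030 + 0.067 = 0.097 at u = 0.3 and 0.070 at u = 0.7. The direction of the possible distortion follows from the design. Its size rests on the assumed utilities, survival gain and SD, and on the assumption that patients who survive under either strategy have the same utility in both arms.

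The issue concerns the quality-of-life secondary endpoint. It does not touch the primary analysis or the sample size.

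**What to change.** In Secondary study parameters, or in the analysis plan if that is where such detail sits, and before any unblinded look at this endpoint:

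- Add a comparison of 6-month EQ-5D-5L utility in all randomised patients with death scored 0, and of EQ-VAS with death given the worst rank. Adjust for center and ECMO mode by a linear model or a stratified rank test.
- Report the survivor-only comparison beside it, labelled as descriptive and not protected by randomisation.
- Keep living patients who could not be reached separate from deaths. A missing questionnaire is not a zero.
- As a minor wording point, name the adjusted forms of the listed tests: a linear model in place of the t-test, Cochran-Mantel-Haenszel or risk-difference regression in place of chi-square, and van Elteren in place of Mann-Whitney.

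The cost is wording. No new data are needed, because 6-month mortality is already collected for the primary endpoint. The downside is that the all-randomised endpoint mixes survival with quality of life, which is why the survivor description stays alongside it.

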### Plans to promote participant retention and complete follow-up {18b}

As mentioned at 11b, crossover to another treatment arm than allocated is allowed and in principle temporary. The timing of reversion is left to the consideration of the treating physician. The crossover will be mentioned in the CRF, and the primary and secondary outcome parameters will be measured and mentioned in the CRF after crossover as well. In case of no informed consent, the patient will no longer be exposed to the allocated study intervention, but consent will be asked to collect the data according to the study protocol. If no informed consent is given for this, the patient will be withdrawn from the study and replaced. Quality of life assessment will be recorded by means of a structured telephone interview. If the patient does not answer the phone, several attempts will be made to contact again.

### Data management {19}

For each randomized patient, a digital CRF will be formed. Central data management will be performed in REDCap (Research Electronic Data Capture) by technicians and data managers of the trial coordination center. Trial data will be entered in the patient’s CRF by the local investigator or research nurse. REDCap gives multiple tools to promote data quality. The project leader will screen REDCap regularly for missing and incorrect data. When present the project leader will contact the local investigator to adjust or complete the eCRF. The data will be kept for at least 25 years.

### Confidentiality {27}

All randomized patients are identified by a patient independence number in combination with a center number. Trial personnel will not pass names outside the local hospital. On screening forms, digital CRF, or other documents submitted to the coordinating center, patients will not be identified by their names but by their numbers. The subject identification code will be safeguarded by the local investigator.

### Plans for collection, laboratory evaluation, and storage of biological specimens for genetic or molecular analysis in this trial/future use {33}

See above 26b; no biological specimen will be collected.

## Statistical methods

### Statistical methods for primary and secondary outcomes {20a}

#### Primary study parameters

The primary analysis will be a single comparison between the treatment groups of the primary outcome measure after 6 months. This analysis will be performed according to the intention-to-treat principle. To assess the effect of treatment with lower anticoagulation targets or LMWH with standard care, an absolute risk reduction of poor outcome and its corresponding 95% confidence interval will be calculated. The confidence interval of the risk reduction will be compared with the non-inferiority marge of 7.5% of both intervention arms adjusted for center and ECMO mode.

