## Objectives {7}

Our primary research question is if anticoagulation with UFH with reduced anticoagulation targets or anticoagulation with low molecular weight heparin (LMWH) leads to a reduction in the occurrence of major bleeding without an increase in thromboembolic complications or a negative effect on outcome compared to the standard practice of high anticoagulation targets with UFH. We expect fewer complications and improvement of survival after ECMO therapy for both interventions.

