## Trial design {8}

We will perform a multi-center phase 3, three-armed, randomized, non-inferiority open-label study in patients receiving veno-venous (VV) and veno-arterial (VA) ECMO therapy. Allocation is in a 1:1:1 ratio.

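### The primary analysis is described as one comparison, but two non-inferiority comparisons with usual care are planned, and the confidence level for each differs or is unclear between the sample-size and analysis sections

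*Protocol article*

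**What the plan says.** The design has one usual-care arm (UFH at the higher aPTT target) and two intervention arms (UFH at a lower target, and LMWH). Trial design {8} says: "Allocation is in a 1:1:1 ratio".

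Under Statistical methods {20a}, Primary study parameters, the article first says: "The primary analysis will be a single comparison between the treatment groups of the primary outcome measure after 6 months". Later in the same paragraph it says: "The confidence interval of the risk reduction will be compared with the non-inferiority marge of 7.5% of both intervention arms", with adjustment for center and ECMO mode. The interval there is a 95% interval for the absolute risk reduction, with sidedness not stated.

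Sample size {14} opens its calculation with: "To show non-inferiority with a significance level (alpha) of 5%, power of 80%, and a non-inferiority limit (delta) of 7.5" percent. The result is that "the corresponding sample size is 91 patients per group". It explains the target as excluding the margin with "the upper limit of a one-sided 95% confidence interval (or equivalently a 90% two-sided confidence interval". Enrolment is then raised to 330, and the reasons given are a smaller effect and drop-outs.

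Objectives {7} asks whether "anticoagulation with UFH with reduced anticoagulation targets or anticoagulation with low molecular weight heparin (LMWH) leads to a reduction" in major bleeding without offsetting harm, and closes by expecting benefit from both interventions. Interim analyses {21b} adds one look at 150 patients, with stopping for non-inferiority at an alpha of 1%.

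**The concern.** Two intervention arms, each judged against a margin relative to the same control, make two primary comparisons. Calling them one leaves two matters unsettled.

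- **What is being compared.** Taken by itself, the opening sentence would also fit a global three-group test or a pooled contrast of both interventions with usual care. Pooling would let one strategy mask the other, and LMWH is a different drug from the lower-target UFH.
- **At what level.** The sample-size section fixes the error rate for one pairwise comparison. The analysis section gives an interval level that may or may not be the same. The error rate over the two comparisons and the power of each both depend on which level applies.

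What is at stake is a claim that a changed anticoagulation strategy is non-inferior on a composite that includes death at 6 months.

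**Working it through.** **Inputs.** From Sample size {14}: event rates 70% (usual care) and 60% (intervention), margin 7.5 percentage points, alpha 5% one-sided, power 80%, 91 per group, 330 enrolled (330/3 = 110 per arm). From Trial design {8}: 1:1:1 allocation. From Interim analyses {21b}: one look at 150 patients at 1%.

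**1. The plan's own figure.** For one intervention against usual care with unpooled variance:

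n = [p_C(1−p_C) + p_T(1−p_T)] × (z_α + z_β)² / (difference + margin)²

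= (0.21 + 0.24) × (1.645 + 0.842)² / (0.10 + 0.075)² = 90.85, rounded up to 91.

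The stated figure reproduces. It does so with the whole one-sided 5% on a single pairwise contrast and nothing reserved for a second one.

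**2. Chance of at least one false non-inferiority claim, final analysis only.** Worst case: both interventions truly sit at the margin. With equal arms and a shared control, the two test statistics have a correlation of about 0.5. The rate is 1 − P(Z₁ < c, Z₂ < c).

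- One-sided 5% each (c = 1.645): 8.8%. With the correlation at 70% versus 77.5%, which is 0.21/(0.21 + 0.174) = 0.546, it is 8.6%. A binomial simulation at those rates gives 8.5% at 91 per arm and 8.8% at 110. The independence value is 1 − 0.95² = 9.75%, and the upper bound is 10%.
- One-sided 2.5% each (two-sided 95% interval, c = 1.960): 4.5%.

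**3. With the interim look.** The probability is extended to two comparisons at two looks. The correlation between looks is √(150/330) = 0.674, the final level is unadjusted, and all 150 patients are treated as evaluable. The article does not say whether the 1% is one- or two-sided, so both are shown (one-sided 0.5% if two-sided). The sample-size re-estimation is left out.

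| Final level per comparison | No look | Look at one-sided 0.5% | Look at one-sided 1% |
|---|---|---|---|
| One-sided 5% | 8.8% | 9.1% | 9.5% |
| One-sided 2.5% | 4.5% | 5.0% | 5.6% |

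**4. Power per comparison.** Power = Φ(0.175/√(0.45/n) − z_α).

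| Evaluable per arm | 0.175/√(0.45/n) | One-sided 5% | One-sided 2.5% |
|---|---|---|---|
| 91 | 2.489 | 80% | 70% |
| 110 | 2.736 | 86% | 78% |

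For 80% power at one-sided 2.5%: 0.45 × (1.960 + 0.842)² / 0.175² = 115.3, so 116 per arm, which is more than the 110 enrolled.

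**The case against.** Several parts of the other side's case stand.

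- **The analysis section may already use the stricter level.** A bare 95% interval is usually read as two-sided. On that reading the rate over both comparisons is about 4.5% before the interim look. A reader might infer that the plan carries a 9% error rate. The article does not support that as a plain statement, because one-sided 5% appears only in the sample-size section. The two-sided reading has its own consequence: the stated 80% power no longer applies.
- **No rule says that one successful arm confirms the trial.** The research question joins the interventions with an *or*, but the text also expects benefit from both. If both arms had to pass, there would be no inflation (1.5% in simulation at one-sided 5% with both at the margin). The article does not state that requirement either.
- **Adjustment is debated.** Many statisticians do not adjust when distinct treatments share a control and each answers its own question. On that view 5% per comparison is defensible. The 8.8% also needs both arms to sit exactly at the margin, whereas the design assumes a 10-point benefit.
- **A multiplicity rule may stand in an analysis plan that is not shown.** Its absence from the article is therefore not held against the plan. The description as one comparison and the two interval statements are in the text shown.
- **Pooling is a weak reading.** A reader might infer it from the opening sentence. The per-group sample size and the later reference to both intervention arms point to pairwise comparisons, and the singular may have been meant as one outcome at one time point. The wording still needs correcting, because it describes a comparison between treatment groups, not a time point.

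**Conclusion.** The point holds in a conditional form. The article describes as one comparison what its design and its own margin rule make two, and it does not fix one confidence level for them.

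The size depends on which section governs. At one-sided 5% each, the worst-case chance of at least one false claim is about 8.8% (9.1–9.5% with the look). With a two-sided 95% interval it is about 4.5% (5.0–5.6% with the look), and the power statement is then too high by about 10 points at 91 per group. The error rates assume that success in either arm supports a claim, that both arms lie at the margin and that they share a control. The power figures assume the planned 70% and 60%.

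This is a correction of wording and of a power statement. It does not show that the design is unsound.

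**What to change.** - In Primary study parameters, replace the singular description with: two separate pairwise comparisons with usual care; the interventions are not pooled.
- Use the same confidence level, with its sidedness, there and in Sample size {14}. A two-sided 95% interval for each comparison keeps the error over both near one-sided 5%.
- Count the interim alpha within that level and say whether the 1% is one- or two-sided. An unadjusted look takes the 4.5% to between 5.0% and 5.6%, so the two-sided 95% interval alone does not guarantee 5%.
- Restate the power for the rule chosen.

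The cost is text only, with no change to conduct. With the two-sided 95% interval, per-comparison power at 110 evaluable per arm is restated from 86% to 78%. It will be lower after drop-outs, since part of the margin between 91 and 110 was meant to cover them. Reaching 80% would need 116 evaluable per arm.

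### The trial is sized on a one-sided 95% limit, but the primary analysis compares an unqualified 95% confidence interval with the margin, so the decision rule and the stated power may belong to different tests

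*Protocol article*

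**What the plan says.** **Planning.** Sample size {14} sets the error rate, power and margin: "To show non-inferiority with a significance level (alpha) of 5%, power of 80%, and a non-inferiority limit (delta) of 7.5"%. It assumes that "the primary composite endpoint will be reached in 60% of patients compared to 70% in usual care", and concludes that "the corresponding sample size is 91 patients per group". It is explicit about the interval: the requirement concerns "the upper limit of a one-sided 95% confidence interval (or equivalently a 90% two-sided confidence interval"). It then adds a reserve: "To compensate for a lower effect and drop-outs, 330 patients will be enrolled". Drop-out is defined there, but no rate is given.

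**Analysis.** Statistical methods {20a}, Primary study parameters, says that "an absolute risk reduction of poor outcome and its corresponding 95% confidence interval will be calculated". The rule follows: "The confidence interval of the risk reduction will be compared with the non-inferiority marge of 7.5"%, for both intervention arms, adjusted for center and ECMO mode. This section says neither one-sided nor 90%.

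**Interim.** Interim analyses {21b} provides for conditional power for non-inferiority against the same margin, and for re-estimation of the sample size if that power is 50–79%. It gives no critical value for the final test.

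Nothing in the article reconciles the planning interval with the analysis interval.

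**The concern.** A non-inferiority test is defined by its margin and by the level of the confidence limit compared with that margin. The article gives that level twice, and the two statements do not match as they would ordinarily be read. An unqualified 95% interval for a risk difference is two-sided, so its upper limit gives a one-sided 2.5% test. The sample size rests on a one-sided 5% test.

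Two things are at stake. First, the stated 80% power and the stated reserve apply to the planning test and not, on the usual reading, to the analysis described. Second, the same data could be declared non-inferior under one section and not under the other. If the level is left open until results are known, it can be chosen with the results in view, in a trial whose clinicians know the allocation. The interim re-estimation has the same gap, because conditional power cannot be computed without the final critical value.

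This is not detail that an article may leave to a fuller document. Both levels are printed here, and the sample size section shows that the distinction was understood.

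**Working it through.** **Inputs.** All are from Sample size {14} unless noted.
- Event rates: 0.70 usual care, 0.60 intervention, so the true benefit is 0.10.
- Margin: 0.075, taken as absolute.
- Power: 80%.
- Enrolment: 330, allocated 1:1:1 (Trial design {8}), so 110 per arm.
- Drop-out: no rate is given; 2%, 5% and 10% are used below as assumptions.

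**Formulas** (normal approximation, unpooled variance).
- Variance term: V = 0.70 × 0.30 + 0.60 × 0.40 = 0.45.
- Distance from truth to margin: 0.10 + 0.075 = 0.175.
- n per group = (z_alpha + z_power)² × V / 0.175².
- Power = Φ(0.175 / √(V/n) − z_alpha).

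**Step 1: reproduce the plan's figure.** One-sided 5%: (1.645 + 0.842)² × 0.45 / 0.175² = 90.9, so **91 per group**. This matches. The same inputs do not give 91 at one-sided 2.5%.

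**Step 2: the two-sided 95% reading.** (1.960 + 0.842)² × 0.45 / 0.175² = 115.3, so **116 per group**, or 3 × 116 = **348** in total, against 330 planned.

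**Step 3: power under each reading.** At n = 110, √(0.45/110) = 0.0640 and 0.175/0.0640 = 2.736. Then Φ(2.736 − 1.960) = 78.1% and Φ(2.736 − 1.645) = 86.2%. The other rows follow in the same way.

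| Evaluable per group | One-sided 95% (two-sided 90%) | Two-sided 95% |
|---|---|---|
| 91 | 80.1% | 70.1% |
| 110 (all 330) | 86.2% | 78.1% |
| 107.8 (2% drop-out, assumed) | 85.6% | 77.3% |
| 104.5 (5%, assumed) | 84.7% | 76.0% |
| 99 (10%, assumed) | 82.9% | 73.8% |

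Exact binomial enumeration at 110 per group with a two-sided 95% interval gives 78.4% (Wald) and 78.5% (Newcombe), so the approximation is not the cause.

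**Step 4: the reserve for a lower effect.** Suppose the true intervention rate is 62% instead of 60%, with 110 evaluable per group. Power is 78.5% under the planning rule and 68.3% under the two-sided 95% rule. The true benefit that gives 80% power at 110 per group is 8.3 points under the planning rule and 10.4 points under the two-sided 95% rule. So 330 leaves room for a smaller effect only under the planning rule.

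**Step 5: where the verdict differs.** At 110 per arm with both observed rates near 70%, SE = √(2 × 0.70 × 0.30 / 110) = 0.0618. The observed benefit needed to pass is z × SE − 0.075:
- two-sided 90%: 1.645 × 0.0618 − 0.075 = 0.027, or 2.7 points;
- two-sided 95%: 1.960 × 0.0618 − 0.075 = 0.046, or 4.6 points.

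**Step 6: dependence on the margin.** Sample size {14} also expresses the limit as 75.25% against 70%, which is 5.25 points (7.5% of 70%). With 0.1525 in place of 0.175, the requirement is 120 per group at one-sided 5% and 152 at one-sided 2.5%. Power at 110 per group is then 77.0% and 66.4%. The 91 reproduces only with the absolute 7.5-point margin, so Steps 1 to 5 use that.

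**The case against.** The strongest reply is that the primary analysis section never says two-sided. The sample size section has already defined the trial's interval as one-sided 95%. If the later 95% interval is that same one, the sections agree, power with 330 evaluable is 86.2%, and only a word is missing. This stands as a limit on the claim: the power loss is conditional on the usual reading. It does not remove the need to say which interval is meant.

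Four further replies have force.
- **The shortfall at full enrolment is small:** 80 − 78.1 = 1.9 points. The 70% figure belongs to 91 per group, which is not the enrolment target.
- **Drop-out may be low.** Patients without consent to data use are replaced (section {18b}), data are kept for those who die before deferred consent could reasonably be obtained (section {26a}), and deaths by 6 months are primary events. A 10% rate is an assumption and not the plan's own figure.
- **330 is not a ceiling.** The interim re-estimation could raise it, and adjustment for center and ECMO mode could change precision. The article quantifies neither, and the re-estimation itself needs the missing critical value.
- **The two-sided 95% reading is the stricter one.** It makes a false claim of non-inferiority less likely, at a modest cost in power.

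A reader might infer that a two-sided 95% interval also takes care of the two intervention comparisons. The document does not support that. One-sided 2.5% per arm bounds the overall error at one-sided 5% only if that is the overall target, and the interim look at the 1% level lies outside it.

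**Conclusion.** The inconsistency is real. The sample size and the primary analysis state the interval level differently, and the pass or fail rule of the primary endpoint depends on which is followed. At 110 per arm and event rates near 70%, observed benefits between about 2.7 and 4.6 points fall in the disputed zone.

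The effect on power is conditional. If the 95% interval is two-sided, the plan needs 116 per group, and the reserve that 330 was meant to provide is gone. If it is one-sided, the reserve is real. A reader might infer that the article simply fails to deliver 80% power, even with every patient evaluable. It does not support that as a flat statement, because the sidedness of the analysis interval is not given and the gap at 330 is under 2 points even on the stricter reading.

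The figures assume 70% v 60%, an absolute 7.5-point margin, no covariate adjustment and no interim change to the sample size. Correction is warranted because the matter is the decision rule itself.

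**What to change.** State one interval level in both Sample size {14} and Primary study parameters, and use the corresponding critical value (1.645 or 1.960) for the conditional power in Interim analyses {21b}. Do this before unblinded data are seen: the interim is planned at 150 enrolled, and the article reports 111 recruited at the time of writing.

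Either of two routes is coherent:
1. **Keep the 95% interval and call it two-sided.** Restate the sample size as 116 per group for 80% power, say that 330 gives about 78% before drop-out, and delete the statement that 330 covers a lower effect and drop-outs.
2. **Keep the planning level.** Write two-sided 90% (one-sided 95%) interval in Primary study parameters. The 91 per group and the reserve then stand.

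Before new figures are written in, reconcile the 75.25% with the 7.5-point margin, since the restated figures hold only for the absolute margin. If a power allowing for drop-out is quoted, label the rate as an assumption and show a range. Deal with the two comparisons and the interim look in their own right, whichever route is chosen.

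The cost is wording and, on the first route, a slightly less favorable power statement. Neither route by itself requires more patients. A full 80% under the first route would take 348 evaluable, 18 more than 330, plus an allowance for drop-out.
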